### Data collection procedure

Data will be collected using multiple methods, namely, 1) a structured questionnaire; 2) hand dust wipe samples from children aged between one and five years; 3) floor and/or windowsill dust wipe samples; and 4) yard soil samples. These methods will be applied in two phases. In phase one, participants will be allocated into either the control or intervention group (see Fig. 1). Both the control and intervention groups will be interviewed, household floor and/or windowsill dust wipes will be taken, yard soil samples collected, and hand dust wipe samples taken from children in participating households. The intervention group will participate in the domestic hygiene demonstration and educational discussion. The intervention group will be allowed a period of three months to apply the domestic hygiene intervention. Each household will be given a diary to record their daily cleaning patterns. During the three months, a monthly reinforcement visit will be undertaken to follow-up and encourage the sustained application of the intervention. In phase two, after three months, both the intervention and control group will be visited to collect a repeat floor and/or windowsill dust sample, yard soil sample and hand dust wipe sample from children. Feedback will be obtained from the intervention group on the experience of the intervention using a checklist.

### Questionnaire-based interview (method 1)

A hard copy structured questionnaire will be administered through an interview with a parent or guardian to obtain information on living conditions, socio-economic status, domestic and personal hygiene practices and potential alternative sources of exposure to toxic metals. The questionnaire has been widely used in South Africa for blood lead surveys conducted by the Environment and Health Research Unit of the SAMRC.

### Hand dust wipe sample (method 2)

Hand dust wipes samples will be collected from assenting children aged between one and five years and/or whose parents/guardians have given consent to participate in the study. Ghost wipes will be used to wipe the hand from the heel of the hand above the wrist up to the fingertips. The left and right will be wiped following the same pattern on both the back and palm of the hand.

### Floor and/or windowsill dust wipe sample (method 3)

Samples of floor and/or windowsills dust will be collected during the baseline and post-intervention visits. The collection methods for floor and windowsill dust will be based on US Department of Housing and Urban Development guidelines for the evaluation and control of lead-based paint hazards in housing [13]. Floor and/or windowsill dust samples will be collected from the room where children spend most of their time. If the room contains a carpet, then floor dust samples will be collected from the kitchen. If there are no windowsills in the house selected, then the floor dust samples will be collected. An area to be sampled will be a rectangle or square measuring one square meter that will be demarcated using a commercial template. Disposable dust wipes will be used to collect dust samples.

### Soil sample collection (method 4)

Soil samples will be collected in the yard of the selected households in both the intervention and control groups (up to a depth of 10 cm) in accordance with the US EPA methods. Surface soil samples will be stored in a transparent plastic bag. To reduce moisture in the collected soil samples, the samples will be dried for 24 h at 40 °C. The samples will be crushed and sieved to a particle size of less than 250 µm.

### The intervention

#### Personal hygiene intervention

At the end of the questionnaire-based interview, blood collection and environmental sample collection, participants (parents/guardians) will be engaged in an educational discussion for approximately 30 min, with the aid of a specially designed educational pamphlet (Fig. 2). The pamphlet contains information about health effects potentially associated with dust exposure from mine dumps and the personal hygiene and domestic hygiene steps that may be followed to reduce dust exposure. The pamphlet will be pre-tested during the pilot study and refined as necessary.

**Fig. 2 Fig2:**
[figure not shown]
Educational pamphlet

#### Domestic hygiene intervention

The researcher, through a demonstration to participants (parents/guardians), will conduct a domestic hygiene intervention. During the demonstration, participants will be guided on optimal cleaning of windowsills, floors and other surfaces with water and detergent, and advised on an appropriate method of cleaning. The Centers for Disease Control and Prevention recommends a continuing program of wet mopping and damp dusting of all hard surface floors, stairs, windowsills and baseboards at least twice a week, to keep lead-contaminated house dust down to a minimum. Participants will be provided with a package of cleaning materials (mop, bucket, detergent, hand wash liquid soap and cloth for wet dusting) which will be used during the demonstration and retained by participants to facilitate the sustainability of the intervention during and after the study. The cleaning materials will be replenished on follow-up visits.

### Data management and analysis

#### Hand dust wipe sample analyses

The samples will be stored in a sealable plastic bag and transported by the research team to a designated laboratory at the Doornfontein Campus, University of Johannesburg for analyses of Lead content.

#### Floor and/or windowsill sample analyses

Each floor and/or windowsill dust sample will be sent by the researcher to a designated laboratory at the Doornfontein Campus, University of Johannesburg for analyses of lead content. Lead dust levels will be determined using inductively coupled plasma mass spectrometry after appropriate sample preparation. The United States Environmental Protection Agency’s dust lead standards, 10 µg/ft^2^ for floors and 100 µg/ft^2^ for windowsills will be applied in this study.

#### Soil sample analyses

Each soil sample will be analysed for lead content for 60 s using an X-ray fluorescence spectrometer, available at the SAMRC Environment and Health unit designated lab. A trained technician at the SAMRC will do the analysis. The mean, median and range of the levels of lead will be recorded for the control and intervention groups. Mathee et al. found severe and extensive lead contamination of garden soil which warranted action to investigate further and protect the health of the affected communities [14].

### COVID-19 health and safety precautions

The study will adopt precautionary procedures to address and mitigate the spread of Covid-19 between field staff and community members/study participants. These procedures will be guided by the ‘COVID-19 OCCUPATIONAL HEALTH AND SAFETY MEASURES IN WORKPLACES COVID-19 (C19 OHS), 2020’, as promulgated by the South African Department of Employment and Labour. Amongst other aspects, if field staff are sick or have symptoms associated with COVID-19 prior to or during data collection, they will not be permitted to participate in data collection and will be instructed to self-quarantine. Field staff members will wear a face mask when reporting for duty and during interactions with study participants. In addition, requests will also be made for study participants to also wear a face mask. If the participant does not have a face mask, the field staff shall provide them with one. The procedure will also take into account the practice of social distancing during field staff interactions, as well as interactions between field staff and study participants by having individuals stand 1.5–2 m apart. Where study activities make social distancing not practicable, field staff members will put on a face shield, in addition to wearing a face mask. Additionally, a hand sanitiser with at least 70% alcohol content will always be present and made available for use by the field staff and study participants. More specifically, field staff members will be required to use the hand sanitiser before and after each interaction with one another and with study participants, as well as clean and disinfect surfaces and equipment that is touched during data collection.

### Data analysis plan

Descriptive statistics such as means, medians, standard deviations, interquartile and 95% confidence intervals will be used to describe lead levels and other continuous outcomes. Frequencies and proportions with 95% confidence intervals will be calculated for categorical variables. The paired t-test will be used to compare the difference in lead levels within groups between baseline and follow-up. The two-sample t-test will be used to compare the mean lead levels between groups. McNemar’s test will be used to compare the children’s health outcomes between baseline and follow-up. The change from baseline to follow-up will be modelled, with a group main effect, with adjustment for other covariates. A linear mixed-effects model will be used to model the change in lead levels resulting from the hand dust wipes, with the main effect for the group. Adjustments will be made for lead levels in homes, as well as other important baseline characteristics, including variables from the administered questionnaire. The model will be adjusted for clustering within the household. Depending on the level of missingness, imputation of follow-up data may be conducted, and analysis rerun as sensitivity analysis. Statistical significance is taken at a 5% level. All analyses will be conducted using STATA 16.

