**Fig. 1 Fig1:**
[figure not shown]
Map of Snake Park showing control and intervention group (source: [name], South African Medical Research Council)

The map of the study area reflecting household street names and stand numbers will be used to stratify single dwellings in close proximity (within 500 m) to the mine dump. Households located in the intervention group will be randomly selected and matched by structure and type (e.g. government-funded houses or non-government funded houses) with a dwelling in the control group.

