### Determination of the sample size

Strata will be defined according to two main divisions within the catchment area. Systematic random samples will be taken within each division where every Xth dwelling will be sampled. Sample sizes were calculated at 80% power. The number of households per group is increased by 5% to account for possible loss to follow-up. To detect a mean difference in change from baseline to follow-up of -3 μg/dL between the control and experimental groups i.e., a lower lead level by 3 μg/dL in the intervention group compared to the control group, with 80% power and common standard deviation of 11 μg/dL, a sample of 213 households per group is required. To account for LTFU the number of households per group is adjusted to 224. Therefore 448 households are to be recruited and randomized to control and experimental groups accordingly.

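### The level-only t-test does not target the change on which the study is sized, and the adjusted change models name neither the outcome's own baseline value nor the dwelling type used for matching

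*Protocol article*

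**What the plan says.** All references are to the protocol article.

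- **Determination of the sample size.** The target is set out as "To detect a mean difference in change from baseline to follow-up" of -3 μg/dL, with a common SD of 11 μg/dL and 80% power. This gives 213 households per group, raised to 224 for loss to follow-up.
- **Data analysis plan, test of levels.** "The two-sample t-test will be used to compare the mean lead levels between groups". The visit is not stated, and no baseline term is involved.
- **Data analysis plan, models.** "The change from baseline to follow-up will be modelled, with a group main effect, with adjustment for other covariates". A linear mixed-effects model of change is planned for the hand wipes. On covariates: "Adjustments will be made for lead levels in homes, as well as other important baseline characteristics, including variables from the administered questionnaire". On dependence: "The model will be adjusted for clustering within the household".
- **Study design and population (text under Fig. 1).** "Households located in the intervention group will be randomly selected and matched by structure and type" with a dwelling in the control group.

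The Data analysis plan does not mention the matched pairs or the matching factor, and it does not say which between-group analysis is the main one.

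**The concern.** The study is sized on one quantity, the between-group difference in change, while one of its stated between-group tests addresses another, the difference in levels. If the groups differ at baseline, part of that difference passes into a comparison of follow-up levels. A change score that is not adjusted for baseline errs in the opposite direction when the imbalance is due to chance. The two analyses can therefore disagree on the same data, and the plan does not say which one decides.

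The change models come closer to the sample-size target. However, the covariates they name do not include the same measure's baseline value. For the hand wipes, lead in the home is a different measurement from the child's own baseline wipe. Dwelling structure and type are built into the selection of households and then not named in the analysis. Precision is at stake, as is protection against baseline imbalance. Both could be had from data the study already collects.

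**Working it through.** **Inputs.** From the sample-size section: difference 3, SD 11, power 80%, 213 per group, 5% allowance for loss. From the Data analysis plan: 5% significance, taken as two-sided because that reproduces the stated figure. Not in the documents, so assumed: correlation r between baseline and follow-up of 0.3, 0.5 or 0.7; equal SDs at the two visits; within-pair correlation ρ from matching of 0 to 0.3.

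**1. The plan's own figure.** n = 2(1.96 + 0.8416)² × 11²/3² = 211.04, so 212 by the normal formula. The t-based solution is 212.01, which rounds up to 213 and matches. 213 × 1.05 = 223.65, so 224, which also matches. A one-sided test would need 167 and does not match. The figure is sound for an unpaired comparison of two means.

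**2. SDs of the three analyses.** With s the SD of a level:
- follow-up level: s
- change score: s√(2(1 − r))
- follow-up level or change, adjusted for own baseline: s√(1 − r²)

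Power = Φ(3 / (SD × √(2/213)) − 1.96). The protocol does not say whether 11 is the SD of levels or of changes, so both readings are shown.

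| Reading | r | Level t-test | Change score | Own-baseline adjustment |
|---|---|---|---|---|
| 11 = SD of levels | 0.3 | 80.4% | 66.2% | 83.9% |
| | 0.5 | 80.4% | 80.4% | 90.1% |
| | 0.7 | 80.4% | 95.3% | 97.6% |
| 11 = SD of change | 0.3 | 91.5% | 80.4% | 93.7% |
| | 0.5 | 80.4% | 80.4% | 90.1% |
| | 0.7 | 58.7% | 80.4% | 86.3% |

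Worked cell, r = 0.5: adjusted SD = 11 × √0.75 = 9.53; SE = 9.53 × √(2/213) = 0.923; 3/0.923 − 1.96 = 1.29; Φ(1.29) = 90%.

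Own-baseline adjustment has the highest power in every row. The level t-test falls below the change score only when r exceeds 0.5.

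**3. Baseline imbalance.** For a chance baseline difference D, the expected error is r × D for follow-up levels, −(1 − r) × D for the unadjusted change score, and about 0 with own-baseline adjustment. At D = 2 and r = 0.5 the errors are +1.0 and −1.0, each one third of the target difference of 3. If 11 is the SD of levels, the standard error of D under randomisation is 11 × √(2/213) = 1.07. D = 2 is then about 1.9 standard errors, towards the edge of what chance gives. An imbalance of one standard error gives an error of 0.5 × 1.07 = 0.53.

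**4. Matching.** If pairing induces a within-pair correlation ρ, the SD for the comparison becomes 11√(1 − ρ). Power at 213 per group is 80.4%, 84.3%, 88.2% and 92.0% at ρ = 0, 0.1, 0.2 and 0.3. Leaving the pairs out costs nothing at ρ = 0 and makes the unpaired test conservative when ρ is positive.

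**5. Does the planned difference survive the change of model?** Write change = a + τ·group + b·baseline. Adding baseline to both sides gives follow-up = a + τ·group + (1 + b)·baseline. The group coefficient τ is identical, so the planned difference of 3 still applies.

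**The case against.** The strongest reply is that the plan already contains what is needed. It has covariate-adjusted models of change, these agree with the sample-size target, and they use baseline by subtraction. The wording on other important baseline characteristics and questionnaire variables could cover own baseline and dwelling type, and a condensed article may leave the full covariate list to another document. This stands in part. A reader might infer that every between-group test here ignores baseline, and the text does not support that. What remains is narrower: a level-only test is stated without a subordinate role, and the two terms that the design most clearly calls for are not among those named.

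Three further readings are tempting and not supported:

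- **That all analyses are on the raw scale and the data are known to be skewed.** No scale is stated for the models, and medians and interquartile ranges are planned. The 5.0 μg/dL in the Background is a reference level for public health action, not this population's mean. Setting the SD of 11 beside it says nothing about skewness. A compulsory log-scale analysis would also turn the planned difference into a ratio, and its advantage would rest on an assumed spread and correlation.
- **That omitting the matching invalidates the test.** It mainly makes it conservative, as step 4 shows.
- **That baseline adjustment is always better.** The sample-size section says households are randomised, while the Data collection procedure refers allocation to the map in Fig. 1. If the groups are areas, own-baseline adjustment and change scores rest on different assumptions, and the change analysis is defensible in its own right.

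**Conclusion.** The point holds in this limited form. The t-test of levels does not address the quantity on which the study is sized, and the adjusted change models name neither own baseline nor the matching factor. Under the assumed correlations of 0.3 to 0.7, own-baseline adjustment gives 84% to 98% power, against 66% to 95% (change score) and 80% (level t-test), if 11 is the SD of levels. If 11 is the SD of change, it gives 94% to 86%, against 80% (change score) and 92% to 59% (level t-test). The gain at r = 0.5 is 10 percentage points on either reading. These figures assume equal SDs at the two visits and no systematic baseline difference between groups. The stated sample size is not in error and need not change. This is a worthwhile improvement in precision and clarity; it does not show that the planned analyses are invalid.

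**What to change.** In the Data analysis plan:

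1. Name the adjusted between-group model as the main analysis.
2. Add as terms the baseline lead level of the same measure and dwelling structure/type (or matched pair). Keep the household effect where several children in a home are sampled.
3. Report the adjusted difference with its 95% confidence interval, and describe the t-tests as descriptive.
4. Keep the change analysis without a baseline term as a sensitivity analysis, because adjustment reduces but may not remove pre-existing differences if the groups are mapped areas.
5. Allow a log-scale analysis as a sensitivity analysis if the data prove skewed, with a rule for zero or undetectable results.

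The cost is wording. Lead is measured at both visits and dwelling type is known from the matching, so no new data are needed. One practical limit is that dust may be taken from floor, windowsill or both, so the plan should say how a home is handled when the two visits do not share a surface. Data collection has begun, so the change should be dated and made before follow-up results are compared between groups.

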## Methods

### Study design and population

A before and after intervention study will be conducted with a control and intervention group. This study follows a descriptive, correlational and experimental design [12]. The study area has a population of 4008 with 1124 households situated in Johannesburg Metropolitan Municipality adjacent to the Durban Roodepoort Deep Mine Dump. Figure 1 shows the intervention and control groups within the study area. The study targets children between the ages of one and five years. Children whose parents have not consented to any part of the research, or children who have not agreed, will be excluded from the study. Only parents/guardians over the age of 18 years will be included in the study.

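### Household clustering is handled only in the mixed model; McNemar's test, and the t-tests if applied to individual children's hand wipes, would treat siblings as independent

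*Protocol article*

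**What the plan says.** The Data analysis plan lists three simple tests. Within groups, "The paired t-test will be used to compare the difference in lead levels within groups between baseline and follow-up". Between groups, "The two-sample t-test will be used to compare the mean lead levels between groups". McNemar's test is assigned to children's health outcomes at baseline and follow-up. None of the three sentences mentions the household.

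For hand wipes the same section plans a regression: "A linear mixed-effects model will be used to model the change in lead levels resulting from the hand dust wipes", with a group effect and covariates. It then says "The model will be adjusted for clustering within the household". One significance level is given for everything: "Statistical significance is taken at a 5% level".

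On units, Determination of the sample size counts and allocates households: "Therefore 448 households are to be recruited and randomized to control and experimental groups accordingly". Study design and population says "The study targets children between the ages of one and five years", and Data collection procedure describes "hand dust wipe samples taken from children in participating households". Neither section, nor the section on the hand dust wipe sample, limits a household to one child.

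**The concern.** Siblings in one home share its dust, its yard soil and its cleaning routine, and they always belong to the same study group. Their lead values are therefore likely to be positively correlated. An ordinary two-sample t-test on individual children ignores this and counts two siblings as two independent observations. The paired t-test and McNemar's test have the same weakness when siblings change in the same direction.

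The authors accept the principle, since they adjust the model for household. That adjustment would have no purpose if every home contributed one child. At stake are confidence intervals that are too narrow and a false-positive rate above the stated 5% for any unadjusted child-level comparison that is reported. For children's health outcomes, McNemar's test is the only method the article names, so no clustered analysis stands beside it.

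**Working it through.** **The plan's own figure.** For a difference of 3 with SD 11, 80% power and two-sided 5%:

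n = 2 × (1.960 + 0.842)² × 11² / 3² = 211.05, or 212 after rounding up. The t-based solution is 212.01, which rounds up to the stated 213. Adding 5% gives 213 × 1.05 = 223.65, or 224 as stated. These figures count households and contain no sibling term. They reproduce and do not bear on this point.

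**Inputs for the check.**
- From the article: household allocation, children aged one to five sampled, no one-child rule, 5% level.
- Assumed, because the article gives neither: the share s of homes with two participating children (the rest have one), 0.2 to 0.4; and the within-household ICC of the analysed value, 0.3 to 0.7.

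**Formulas.**
- Size-weighted children per home: m = (1 − s + 4s) / (1 + s)
- Design effect: DEFF = 1 + (m − 1) × ICC
- Understatement of the naive standard error: 1 − 1/√DEFF
- True two-sided error of a nominal 5% between-group test: 2 × [1 − Φ(1.96/√DEFF)]

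For s = 0.2, m = 1.6/1.2 = 1.33. For s = 0.4, m = 2.2/1.4 = 1.57.

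| s | ICC | DEFF | Standard error too small by | True error |
|---|---|---|---|---|
| 0 | any | 1.00 | 0% | 5.0% |
| 0.2 | 0.3 | 1.10 | 4.7% | 6.2% |
| 0.2 | 0.7 | 1.23 | 10.0% | 7.8% |
| 0.4 | 0.3 | 1.17 | 7.6% | 7.0% |
| 0.4 | 0.7 | 1.40 | 15.5% | 9.8% |

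**Simulation.** Ordinary two-sample t-tests were simulated under no group difference, with 213 households per group, whole households allocated and 4,000 repetitions per setting.
- 80% of homes with one child and 20% with two: rejection rates of 6.2%, 6.5% and 7.7% at ICC 0.3, 0.5 and 0.7. This agrees with the formula.
- 60%, 30% and 10% of homes with one, two and three children: 7.8% to 11.8% over the same ICC range. A few larger sibling groups would push the error above the table.

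**Scope.** The table applies to the between-group test on individual children. For the paired t-test the relevant quantity is the sibling correlation of changes. For McNemar's test it is the correlation between siblings in the direction of change of a binary outcome. Neither need equal the ICC of lead levels, so no error rate is given for those two tests. Their direction is the same if the correlation is positive.

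**The case against.** The strongest reply is that the article never says the t-tests will be run on hand wipes. Both sentences speak of lead levels in general. The study also measures floor or windowsill dust and yard soil, which are sampled from the home and raise no sibling problem. The only method assigned to hand wipes by name is the mixed model, and that model is adjusted for household. The sample size is counted in households, and the abstract's Discussion frames the aim as lower indoor dust lead. A coherent reading is therefore simple tests for household measures and a clustered model for the child measure.

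This stands, and it makes the point about the t-tests conditional. A reader might infer that the plan commits to child-level t-tests on hand wipes with standard errors that are certainly too small. The article supports neither half: it does not name the outcome, and the bias depends on sibling numbers and correlation that it does not report. Nor should a reader infer that the t-tests take precedence because they are listed first. Order is not primacy, and a condensed article may leave the choice of primary analysis to the full protocol or SAP.

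The reply does not remove the point. Nothing excludes hand wipes from the t-tests. McNemar's test is assigned to children's outcomes explicitly, and no clustered alternative is named for them. Nor is this only detail deferred to another document: the article names the tests, recognises clustering and attaches the correction to the model alone.

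**Conclusion.** The point holds in conditional form. As written, the clustering adjustment covers the mixed model only. McNemar's test on children's outcomes is exposed, as are the paired and two-sample t-tests wherever they are applied to individual children. The bias arises only if some homes contribute more than one child and siblings' values or changes are positively correlated. The household term in the model suggests the authors expect the first, and shared exposure makes the second plausible.

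Under the assumed ranges, the true error of a nominal 5% between-group test on individual children is about 6% to 10%. With one child per home it stays at 5%. The consequence is modest if the mixed model carries the hand-wipe conclusion. A correction is still worth making before analysis, because it is nearly free and extends a principle the plan already applies.

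**What to change.** Amend the Data analysis plan in three places:

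- **t-tests:** state that they apply to household-level measures (dust and soil, analysed once per household). If they are also wanted for hand wipes, run them on one value per household per visit, the household mean.
- **Hand-wipe group comparison:** take it from the linear mixed-effects model already planned, with its household adjustment.
- **Children's binary health outcomes:** replace McNemar's test with a cluster-robust or household-level method.

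The cost is a sentence or two of text and a small change in analysis code. No new data are needed. Intervals for the child-level comparisons become slightly wider. It would also help to report the number of participating children per household, so that readers can judge how much clustering matters.
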